#### Travel diaries

A travel diary is being completed by all participants on a monthly basis. This is in the form of a calendar with the participants entering the number of journeys made on the calendar for that particular day. In addition, in order for the study team to assess safety, participants indicate when they have had a fall on a particular day. The participant is provided with 12 calendar months’ worth of travel diary. Training is provided at baseline assessment in the completion and return of the travel diaries. At the end of each month participants are asked to return that month of the calendar to the research team. A reminder letter is sent to the participant, along with a reply paid envelope, a short time before the previous month’s diary is due for return.

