### Assessment of safety and adverse events

The main risk associated with this intervention is an increased risk of falling, as participants are being encouraged to become more mobile. So, as all falls will be self-reported on the travel diary, the only adverse events we will record will be any falls within the intervention group that required the assistance of a healthcare professional. To capture these events the therapist will ask, subsequent to the first visit, “Have you had any falls since my last visit?” The occurrence of a serious adverse event as a result of participation within this study is not expected so no serious adverse event data will be collected.

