### Trial management

The trial will be managed by the Trial Management Group. The Trial Steering Committee and Data Monitoring Committee will be combined as a risk assessment has been completed and as the risk to participants is low we consider that the two committees will work best if they are merged. This will be called the Trial Steering and Data Committee (TSDC). The TSDC will meet independently prior to the start of the study and will agree to terms of reference and will monitor unblinded data and the conduct of the study. Only the TSDC will have access to unblinded data until the final outcome assessment has been completed. The TSDC will recommend discontinuation of the study if significant ethical or safety concerns arise or if there is very clear evidence of benefit (clinical or statistical) prior to completion of the study. The sponsor is the University of Nottingham, which will clarify with the funding body (the HTA) and local centre research and development departments their precise responsibilities. The CI, delegated by the Sponsor, is responsible for the proper conduct and management of the trial.

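### Falls that needed a healthcare professional are ascertained only in the intervention arm, so the more serious falls cannot be compared between arms

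*Protocol article*

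**What the plan says.** All references are to the protocol article.

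- **Assessment of safety and adverse events** identifies the harm: "The main risk associated with this intervention is an increased risk of falling, as participants are being encouraged to become more mobile". It notes that falls reach the trial by another route, "as all falls will be self-reported on the travel diary", and then limits the adverse-event record: "the only adverse events we will record will be any falls within the intervention group that required the assistance of a healthcare professional". The source is a question the therapist puts at visits after the first, about falls since the previous visit. On serious adverse events, the section says none is expected from taking part, "so no serious adverse event data will be collected".
- **Travel diaries** describes the other route. "A travel diary is being completed by all participants on a monthly basis", twelve months of diary are supplied, and "in order for the study team to assess safety, participants indicate when they have had a fall on a particular day".
- **Intervention group** and **Control group** set the contact pattern. The intervention arm has up to 12 sessions over four months and may stop sooner if the participant wishes. The control arm has advice and leaflets at the baseline visit.
- **Health economics** collects primary and secondary health care use from the 6- and 12-month assessments.
- **Trial management** gives the combined steering and data committee (TSDC) a safety role: "The TSDC will recommend discontinuation of the study if significant ethical or safety concerns arise".

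**The concern.** Falls that bring in a healthcare professional are the more serious form of the harm the article itself names. The article makes them its only recorded adverse event and then ascertains them in one arm. This is a stated rule about what is collected, not a detail left to another document. An analysis plan can choose a model, but it cannot create control-arm data that were never gathered.

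People who have had a stroke will have some falls needing help whatever arm they are in. Without the control rate, a count from the intervention arm cannot be divided into background and excess. Set beside an empty control column in a report, it could be misread as harm, or dismissed as background when it is not. All-fall counts do not settle the matter, because two arms with similar numbers of falls could differ in how many were serious.

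**Working it through.** **1. Who is asked what, and for how long**

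| Item | Intervention arm | Control arm | Period |
|---|---|---|---|
| Any fall, by day (travel diary) | Yes | Yes | 12 months |
| Fall needing a healthcare professional (therapist's question) | Yes | No | After the first visit to the last visit, at most 4 months |
| Serious adverse events | Not collected | Not collected | – |
| Health care use (questionnaires) | Yes | Yes | 6 and 12 months; no link to falls stated |
| Death (central register) | Yes | Yes | 6 and 12 months |

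The second row has no comparator. It also covers at most 4 of 12 months, one third of follow-up, and less where therapy ends early. A fall after the last visit, or one that ends therapy, has no later visit at which it could be elicited. The diary row is symmetric, but as described it records that a fall happened and not whether help was needed. The health care use row is symmetric, but is not said to identify care given because of a fall.

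**2. Size of the gap for falls needing help**

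The article states no figure for falls, so there is none to reproduce. From Sample size and justification: 253 per arm. Assumption, not from the document: 5% to 15% of participants have such a fall over four months, the same in both arms. Counting one event per affected participant:

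- Intervention arm: 253 × 0.05 = 12.65, about 13; 253 × 0.15 = 37.95, about 38.
- Control arm: 0 recorded, by design.
- Excess if the true ratio were 1.5: 0.5 × 12.65 = 6.3, about 6; 0.5 × 37.95 = 19.0, about 19.

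The excess cannot be identified. A 5% background with a ratio of 1.5 gives 253 × 0.05 × 1.5 = 19.0 events. A 7.5% background with no effect gives 253 × 0.075 = 19.0 events. The record is the same in both cases.

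**3. What the diaries can already show**

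Take 253 × 0.8 = 202 per arm after the article's 20% attrition. Assume 0.5 to 1 fall per person over six months and a negative binomial dispersion of 2 (both assumptions).

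SE(log rate ratio) = √[2 × (1/(202μ) + 2/202)]

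- μ = 1: SE = 0.172; 95% limits a factor of exp(1.96 × 0.172) = 1.40 either side.
- μ = 0.5: SE = 0.199; factor 1.48.

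On proportions with at least one fall, assuming 20% to 50% in controls and 202 per arm, power for a 15-point increase is about 86% to 93%, for 10 points about 52% to 64%, and for 5 points about 17% to 22%. Clustering by therapist is ignored throughout. A comparison of all falls is therefore feasible, but weak for small increases.

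**4. What symmetric capture of falls needing help would give**

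With the same assumed risk p in both arms and n = 253 per arm, SE(log risk ratio) = √[2(1 − p)/(np)].

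- p = 0.05: √(1.90/12.65) = 0.388; factor exp(1.96 × 0.388) = 2.14.
- p = 0.15: √(1.70/37.95) = 0.212; factor 1.51.

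The comparison would be imprecise over four months, but it would exist. At present there is none.

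**The case against.** The strongest objection is that the harm named is falling in general, and falls in general are collected prospectively, with one instrument, in both arms, for a stated safety purpose. The one-arm record adds to the diary and does not replace it; the sentence that sets the rule opens by pointing to the diary. This stands. A reader might infer that the trial cannot say whether the intervention increases falling. The documents do not support that: all-fall incidence is comparable, subject to unblinded self-report and diary return.

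Two further inferences also fail.

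- A reader might fault the article for describing no between-arm analysis of diary falls. It says a full data analysis plan has been agreed and that it summarises a longer protocol, so that detail may properly sit elsewhere.
- A reader might conclude that the TSDC sees only one-sided safety data. Trial management says it monitors unblinded data and does not confine it to the adverse-event record. Diary falls and deaths exist for both arms.

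It can also be said that the fall rates used above are assumed, and that a new form item comes late, since identification of participants ran to July 2011 and final follow-up is August 2012. Both are fair. The first affects the size of the gap and not its existence. The second limits how much can be recovered.

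None of this reaches the remaining point. Neither the diary nor the resource-use questions is described as showing whether a fall needed professional help, and controls are not otherwise asked.

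**Conclusion.** The concern holds for the more serious falls only. As written, falls needing a healthcare professional are recorded in one arm, for at most four months of a twelve-month follow-up, with no serious adverse event data to fall back on. No between-arm comparison of them can be made. On an assumed 5% to 15% four-month risk, about 13 to 38 events would appear in one arm and none in the other under no effect, and an excess of 6 to 19 events (ratio 1.5) could not be told from background.

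The structural finding rests on the article's text alone. The counts rest on the assumed risks, on one event per affected participant and on full numbers per arm. The finding would fall away if the full protocol's diary or questionnaires already ask both arms whether a fall needed help; nothing in the article says that they do.

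**What to change.** 1. Amend Assessment of safety and adverse events so that help from a healthcare professional after a fall is captured with the same question, in both arms, over the same period. Use a mark beside the diary fall entry or an item in the 6- and 12-month questionnaires.
2. Make falls from the both-arm diaries and questionnaires the comparative safety measure, reported by arm to the TSDC and in the final report.
3. Keep the therapist-elicited falls as intervention-arm information. Label them non-comparative and do not table them against an empty control column.
4. State the date on which the new item came in and how much follow-up preceded it.

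The cost is one item on forms already in use and one table by arm, with no new visits. The drawback is timing. Follow-up completed before the change, including many treatment periods, would be covered by recall or not at all, and the report should say so. Where the item cannot be introduced in time, points 2 and 3 can still be applied, using all-fall diary data as the comparison and stating plainly that the more serious falls were not compared.

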### Participant removal from the study due to adverse events

Any participant who experiences an adverse event may be withdrawn from the study at the discretion of the Investigator.

### Procedures for missing, unused and spurious data

Initially a complete case analysis will be performed for the primary and secondary outcome measures and a sensitivity analysis will then be performed in which missing dependent and independent variable data will be replaced using multiple imputations. Missing data will be imputed separately for the intervention and control groups.

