#### Comparisons between treatment arms

Analyses will be undertaken on an intention to treat basis in that participants will be analysed in the group to which they were randomised regardless of whether they received the intervention or not. Two-sided tests will be used to test statistical significance at the 5% level.

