### Assessment of efficacy

#### Analysing primary outcomes

The mean Social Function score of the SF-36v2 will be compared between treatment arms using a multiple membership form of mixed effects, multiple regression analysis adjusting for centre (as a fixed effect), age and baseline Social Function score as covariates and therapist as a multiple membership random effect. Regression coefficients and 95% confidence intervals will be presented. The robustness of these findings will be assessed by repeating the analysis and including baseline variables (such as gender) that are associated with the outcome variable as covariates in the model.

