#### Analysing secondary outcomes

The outcome variables mobility measured with the Rivermead Mobility Index [8] number of outdoor journeys taken, functional ability measured by the Nottingham Extended Activities of Daily Living Scale [19]; mood and carer psychological distress measured by the General Health Questionnaire 12 [9] will be analysed using the same method as for the primary outcome measure. In all analyses, an adjustment for centre, therapist effect, age and baseline value will be made.

The proportion of participants saying they get out of the house as often as they would like will be compared between treatment arms using a mixed effects logistic regression analysis adjusting for centre (as a fixed effect), age and whether or not they get out of the house as often as they would like as recorded at baseline. Odds ratios and 95% confidence intervals will be presented.

The robustness of the findings for all secondary outcomes will be assessed by repeating the analysis and including baseline variables, (such as gender), that are associated with the outcome variable as covariates in the model.

We acknowledge the potential for type 1 errors associated with significance testing for multiple end points. We will, therefore, consider our analyses of the secondary outcome measures to be partly exploratory in nature, and partly confirmatory of our findings for the primary outcome measure.

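### The complete-case main analysis leaves out observed outcomes when the baseline covariate is missing, and a robustness model whose added covariates have gaps would run on a smaller sample than the result it checks

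*Protocol article*

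**What the plan says.** The section on missing, unused and spurious data sets an order: "Initially a complete case analysis will be performed for the primary and secondary outcome measures". A sensitivity analysis follows, in which "missing dependent and independent variable data will be replaced using multiple imputations". It adds: "Missing data will be imputed separately for the intervention and control groups".

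The section on analysing primary outcomes gives the main model as a mixed regression "adjusting for centre (as a fixed effect), age and baseline Social Function score as covariates and therapist as a multiple membership random effect". Robustness is then judged by "repeating the analysis and including baseline variables (such as gender) that are associated with the outcome variable as covariates in the model".

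The section on analysing secondary outcomes carries both features over: "In all analyses, an adjustment for centre, therapist effect, age and baseline value will be made", and "The robustness of the findings for all secondary outcomes will be assessed by repeating the analysis and including baseline variables". Carer GHQ-12 is among these outcomes.

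The section on comparisons between treatment arms describes intention to treat: "participants will be analysed in the group to which they were randomised regardless of whether they received the intervention or not".

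**The concern.** Read together, these sections decide what happens to someone who returns the six-month questionnaire but has no baseline score. The main model needs that score, the complete-case rule does not fill it, and the observed outcome is not used. The person returns only in the multiple-imputation analysis. That analysis also imputes missing outcomes, so it does not isolate the effect of having dropped people for a missing covariate.

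The exclusion is avoidable. A value fixed before randomisation cannot be affected by allocation. Filling it without using arm or outcome therefore does not bias the randomised comparison, and the observed outcome is kept.

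The second consequence concerns the robustness models. Under the same rule, each added baseline variable with gaps removes more people. If the estimate then moves, the reader cannot tell from the two fitted models alone whether adjustment or the change of sample moved it.

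Participants' baseline forms were completed with the research assistant present, so gaps there are probably few. Carer GHQ-12 has less protection: the carer is approached only if there is one and the participant agrees, and completing the form stands as consent. A carer could supply a six-month score without a baseline one.

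**Working it through.** **Inputs.** From the sample size section: 506 participants, 20% attrition, SD 28.2, difference 12.5, 90% power, two-sided 5%, 15 centres, centre ICC 0.04. Allocation is 1:1. The article gives no rate of missing baseline data, so every such rate below is an assumption.

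**1. The plan's own figure.** n per arm = 2 × (1.960 + 1.282)² × 28.2² / 12.5² = 106.96, so 107. Then 107 / 0.8 = 133.75, so 134. The t-test version needs 108, and 108 / 0.8 = 135, the stated figure. The inputs are read as intended.

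**2. Precision of the primary comparison.** Expected outcomes: 506 × 0.8 = 404.8. If a share f of these lacks the baseline score, N = 404.8 × (1 − f), and the half-width is 1.96 × 28.2 × √(4/N). This ignores clustering and baseline adjustment.

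| f (assumed) | dropped | N | 95% half-width |
|---|---|---|---|
| 0% | 0 | 404.8 | 5.49 |
| 1% | 4 | 400.8 | 5.52 |
| 2% | 8 | 396.7 | 5.55 |
| 5% | 20 | 384.6 | 5.64 |

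**3. Power.** Patients per arm per centre: 404.8 / 30 = 13.49. Design effect with the centre ICC alone: 1 + 12.49 × 0.04 = 1.50. Effective n per arm: 202.4 / 1.50 = 135. Power = Φ(12.5 / (28.2 × √(2/135)) − 1.96) = Φ(1.68) = 95.4%. The same steps give 95.1% at f = 2% and 94.0% at f = 10%. The article does not say how its two ICCs were combined, so only the differences between these figures matter here.

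**4. How much a simple fill recovers.** A person with a filled baseline score adds an outcome without covariate adjustment. With an assumed baseline–outcome correlation of 0.5, the variance of the complete-case estimate relative to the filled one is [0.75/(1 − f)] / [0.75(1 − f) + f]. This is 1.014, 1.035 and 1.075 at f = 2%, 5% and 10%. A simulation with 404 participants and baseline scores missing completely at random gave 1.015, 1.033 and 1.075. At 5% missing, the complete-case interval is thus about √1.035 − 1 = 1.7% wider.

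**5. Robustness models.** With k added covariates, each missing a share g independently, the loss is 404.8 × (1 − (1 − g)^k).

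- k = 3, g = 3%: 404.8 × (1 − 0.97³) = 35 people (8.7%).
- k = 3, g = 5%: 404.8 × (1 − 0.95³) = 58 people (14.3%).
- If the same people miss all three: 404.8 × 0.03 = 12, or 404.8 × 0.05 = 20.
- If the added covariate is complete: none.

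**6. Shift from the change of sample alone.** If a random share L is lost, the difference between subset and full-sample estimates has variance V/(1 − L) − V, with V = 4 × 28.2² / 404.8 = 7.86.

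- L = 10%: √(8.73 − 7.86) = 0.93 points.
- L = 15%: √(9.24 − 7.86) = 1.18 points.

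These use the unadjusted SD. Both models adjust for baseline, so at correlation 0.5 they shrink by √0.75, to about 0.81 and 1.02 points.

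**The case against.** The strongest reply is that this is a conventional choice with a safeguard. The plan does deal with missing covariates, since the imputation analysis covers them explicitly. The document is a condensed article that mentions a full analysis plan, and how a stray missing baseline value is filled is usually settled there. Age group and site are stratification factors, and baseline forms were completed under supervision, so few people would be affected.

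Much of this stands. It limits the size of the point and rules out any claim that missing covariates were overlooked. It does not remove the point, because the article does not leave the main-analysis rule open: it states complete case first and covariate imputation only as sensitivity. The article's silence on a common sample is not an error in itself. The differing samples are a consequence of that stated rule.

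Four stronger readings are tempting and are not supported:

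- **Every robustness model is smaller.** This happens only where an added covariate has gaps. The only one named is gender, which may well be complete.
- **The rule contradicts intention to treat.** The article defines that principle as analysis by allocated group. It does not promise that every observed outcome enters every model.
- **The robustness check can never separate adjustment from sample.** Refitting the main model on the reduced sample would separate them, and nothing in the article prevents that.
- **The large losses in step 5 are expected.** They need three unnamed covariates with independent gaps. Items collected at one visit may be missing together, which loses fewer people.

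**Conclusion.** The point holds as a free improvement of low severity. The stated rule leaves observed follow-up scores out of the main result when the baseline value is missing. It also lets a robustness model with incomplete covariates run on fewer people than the analysis it checks.

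In the primary model the cost is minor: 0.03 to 0.15 points of half-width at an assumed 1% to 5% missing, and power of 95.1% rather than 95.4% at 2%. No one should infer that the trial is underpowered because of it. For the robustness models, a 10% to 15% loss would by itself move the estimate with an SD of about 0.8 to 1.2 points, under a tenth of the 12.5-point target difference. That range rests on assumed missing rates, data missing at random with respect to the outcome, and either an assumed correlation of 0.5 or the unadjusted SD. The case rests on avoidable exclusion and on a clean comparison between models, not on lost power.

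**What to change.** Amend the section on missing, unused and spurious data, or the analysis plan, as follows:

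- The main analysis set is all randomised participants with the outcome observed (for carer GHQ-12, all carers with the outcome observed).
- Missing baseline covariates are filled by a simple method blind to arm and outcome, for example the centre mean or a missing indicator.
- Main and extended models are fitted to the same participants.
- Multiple imputation for missing outcomes remains the sensitivity analysis. The rule of imputing by arm applies there and not to the simple baseline fill.

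The cost is a few lines of text and trivial programming, with no new data. The article says the six-month data will not be analysed until all study data are collected, so the change can be made before any results are seen.

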### Compliance

Compliance in this trial will be completion and returning of all diaries and questionnaires. In practice this means 12 monthly travel diaries and three sets of assessment questionnaires, one each at baseline, 6 months and 12 months.

